### Quality assurance

2.10

We will set qualification standards to make sure that patients are treated in according with this trial. Therefore, we will inform all practitioners of the details of this trial. Treatment will be performed by doctors of Korean medicine who have extensive clinical experience with acupuncture and moxibustion. Specifically, they will be graduates of a 6-year full-time course in Korean Medicine, taught as a college program, certified by the Korean Ministry of Health and Welfare as a Korean Medicine Doctor, and have more than 1 year of postgraduate clinical training in a Korean Medicine hospital. Compliance of herbal medicine, acupuncture, and moxibustion should be in the range of 80% to 120% per visit. In this trial, only subjects with compliance of 70% or more will continue the study.

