### Design/setting

2.2

This study was designed as a multicenter, single-arm prospective clinical trial. All participants included will be from 3 hospitals: Dongguk University Ilsan Korean Medicine Hospital, Kangdong Kyunghee Korean Medicine Hospital, and Wonkwang University Kwangju Korean Medicine Hospital. Participants will be recruited through advertisements on bulletin boards at each medical center. The total target sample size is 100 subjects. All participants will voluntarily sign an informed consent agreement. Moreover, all participants will be enrolled after screening via the inclusion/exclusion criteria. All recruited patients will perform related surveys and tests, and be provided with treatments (herbal medicine, acupuncture, moxibustion). They will undergo an approximately 4 menstrual cycle treatment period and a 3 menstrual cycle observation period. If pregnancy occurs during the study, we will offer the herbal medicine to participants for about 15 days. The costs spent (transportation, time, care) in the previous treatment of the participants of this clinical trial will be investigated and compared with the conversion cost of this trial.

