#### Acupuncture and moxibustion

2.5.2

All patients will receive acupuncture treatment on 14 acupoints, GV20, CV4, bilateral Ex-CA7, ST29, SP6, SP9, ST36, and PC6 using acupuncture needles 0.3 mm in diameter and 30 mm in length (Dong Bang, Gyeonggi-do, Korea). At GV20, practitioners will insert needles 5 mm into the scalp fascia. At other acupoints, needle insertion will be to a depth of 15 to 20 mm, depending on the region of the body into which the needles were inserted. These procedures will elicit de-qi sensation. We will use electro-acupuncture for maintain de-qi and infrared therapy to heat the lower abdomen. The electro stimulation will be administered for 20 minutes at low-continuous 2 Hz. Following elicitation of the de-qi sensation at CV4, we will apply moxibustion for 20 minutes. Acupuncture and moxibustion treatments will be performed at MCD 3, 8, and 14 during 4 menstruation cycles. If the patient becomes pregnant during treatment, these treatments will be stopped.

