#### Primary outcome

2.6.1

The primary outcome of this study will be CPR. Clinical pregnancy was considered to be at least 1 gestational sac with fetal heart activity confirmed by ultrasound scan 5 to 6 weeks after pregnancy.^[18]^

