#### Sample size

2.6.3

We did not follow the general method to calculate sample size. The sample size of this study was determined by Ministry of Health and Welfare and Korean Health Industry Development Institute in accordance with study budget, period, and purpose. A total of 100 participants will be recruited, of which 5 will be 20 to 29 years old, 40 will be 30 to 35 years old, 40 will be 35 to 39 years old, and 15 will be 40 to 44 years old. The detail sample size is shown in Table 2, the number of participants by age is based on report of age of the National Supporting Program for Infertile Couples Analysis and Evaluation of supporting project for infertile couples in 2012.^[21]^ Age distribution of participants supported by IVF is shown in Table 3.

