### Statistical analysis

2.8

The analysis set will comprise a full analysis set and a per-protocol set. Descriptive analyses including the mean, standard deviation, and frequency will be undertaken describing the baseline characteristics of participants. Continuous variables of primary and secondary outcomes will be presented in descriptive statistics and categorical data will be presented in frequency and percentage. When comparing and analyzing according to the level of specific variables such as demographic variables, continuous data will be tested using a Student's *t*-test or Wilcoxon's rank sum test. Categorical data will be analyzed using a chi-squared test or Fisher's exact test. For before and after comparisons, a paired *t*-test or Wilcoxon's signed rank test will be used. Repeated measures ANOVA will also be performed, whereas McNemar's test will be performed on categorical data. All statistical analyses will be conducted at a significance level of 0.05 and tested on both sides. Statistical analysis will be performed using the SAS program (version 9.4; SAS Institute Inc., Cary, NC).

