#### Missing data

2.8.1

Upon analysis of the validation variables, if the data are missing at some point or the subject is missing, the last observation carried forward (LOCF) analysis will be performed as if it were obtained at that time. The LOCF analysis applies to all validation analyses.

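### Women below 70% compliance leave the study with no stated pregnancy follow-up, so the clinical pregnancy rate of all enrolled women cannot be observed

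*Protocol article*

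**What the plan says.** Section 2.10 (Quality assurance) gives two compliance figures in consecutive sentences. The first is "Compliance of herbal medicine, acupuncture, and moxibustion should be in the range of 80% to 120% per visit". The second is "In this trial, only subjects with compliance of 70% or more will continue the study". The article does not say whether the 70% applies per visit, per cycle or cumulatively, or how herbal medicine, acupuncture and moxibustion are combined.

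Section 2.6.1 states "The primary outcome of this study will be CPR", with ultrasound confirmation of a gestational sac and fetal heart activity. Section 2.2 sets the observation window: "They will undergo an approximately 4 menstrual cycle treatment period and a 3 menstrual cycle observation period". Section 2.8 adds "The analysis set will comprise a full analysis set and a per-protocol set", without linking either compliance figure to a set. Section 2.8.1 prescribes last observation carried forward for missing data: "The LOCF analysis applies to all validation analyses".

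**The concern.** Compliance is measured after enrolment, and the 70% sentence makes it a condition for staying in the study rather than a criterion for one analysis set. A woman removed in cycle 2 could still conceive in cycles 3 to 7, but the article describes no way for that pregnancy to be recorded. No later analysis can recover an event that was never observed.

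Compliance also depends on the outcome. Acupuncture and moxibustion stop at pregnancy (section 2.5.2). A woman who conceives in cycle 1 therefore has far less scheduled treatment in which to fall below 70% than one who is treated for all four cycles. Removal falls mainly on women who have not conceived, even if compliance has nothing to do with fertility.

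The design gives no protection. There is one arm, and the Discussion says that literature on assisted reproduction will stand in for a control group. No concurrent arm suffers the same loss, so an error in CPR passes straight into the effectiveness and cost-effectiveness comparisons, which are meant to inform national policy.

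**Working it through.** **Inputs from the article.** Continuation limit 70% and per-visit range 80% to 120% (2.10); 4 treatment and 3 observation cycles (2.2); 3 acupuncture and moxibustion sessions per cycle, 12 in all (2.5.2); herbal medicine twice daily on cycle days 3 to 12 and 13 to 28 (2.5.1); 100 women, as 5 + 40 + 40 + 15 (2.6.3). The article gives no expected CPR and no expected share below 70%, so there is no figure of its own to reproduce on this point.

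**Assumptions.** Conception probability p = 3% per cycle. In each of the 4 treatment cycles, a woman who has not conceived is removed with probability q = 2%, 5% or 10%, unrelated to fertility. There is no removal after conception or in cycles 5 to 7. Every conception is counted as a clinical pregnancy.

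**Step 1: CPR with everyone followed.** 1 − (1 − p)^7 = 1 − 0.97^7 = 19.2%.

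**Step 2: CPR under the rule.** Let a = (1 − p)(1 − q) and G = (1 − a^4)/(1 − a).
- Observed pregnancies per woman enrolled: C = pG + a^4 × [1 − (1 − p)^3]
- Share removed: R = q(1 − p)G
- Removed women counted as failures: C. Retained women only: C/(1 − R).

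For q = 5%: a = 0.97 × 0.95 = 0.9215, a^4 = 0.7211 and G = 3.553. Then C = 0.1066 + 0.7211 × 0.0873 = 0.1696, R = 0.05 × 0.97 × 3.553 = 0.1723, and C/(1 − R) = 0.1696/0.8277 = 0.205.

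| q per treatment cycle | Removed, of 100 | Retained only | Counted as failures | Shift from 19.2% (points) |
|---|---|---|---|---|
| 2% | 7 | 19.7% | 18.3% | +0.5 / −0.9 |
| 5% | 17 | 20.5% | 17.0% | +1.3 / −2.2 |
| 10% | 32 | 22.0% | 15.0% | +2.8 / −4.2 |

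**Step 3: if compliance is related to prognosis.** Let d be the share removed, c the CPR in retained women, and r the ratio of the CPR that removed women would have shown to c. Full follow-up gives (1 − d)c + d·r·c; carrying forward as not pregnant gives (1 − d)c; retained women only gives c. With d = 20% and c = 20%, these are 16.0% to 20.0% (r from 0 to 1), 16.0% and 20.0%. For d from 5% to 30% at c = 20%, the gap between the two available figures, d × c, runs from 1.0 to 6.0 points. Carrying forward can never exceed the full-follow-up value. Retained-only is at or above it when r ≤ 1.

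**Step 4: what 70% means.**
- Sessions over 12: missing 2 is 10/12 = 83.3%, missing 3 is 9/12 = 75.0% (below 80% but continues), missing 4 is 8/12 = 66.7% (does not continue).
- Sessions read per cycle: missing 1 of 3 is 66.7%, already below the limit.
- Pooled with herbal doses: (10 + 16) days × 2 = 52 doses per cycle, so one missed session is 54/55 = 98.2%.

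The same missed session can therefore remove a woman or leave her almost fully compliant, depending on a definition that the article does not give.

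**The case against.** The strongest reply is that this is one sentence in a condensed article, placed under Quality assurance. Continuing the study may have meant continuing treatment, the full protocol may provide follow-up after discontinuation, and the visit charts (Tables 4 and 5) are not visible. It stands that one cannot be certain later pregnancies go unrecorded. But the sentence states a rule about the study, and nothing in the visible text limits it to treatment.

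A reader might infer three stronger things, and the document supports none of them.
- That the two compliance figures contradict each other. The first is worded as a per-visit target and the second as a floor for continuing; a woman at 75% can miss the one and meet the other. They are unreconciled and undefined, not incompatible.
- That the reported CPR will be inflated. A full analysis set is planned and last observation carried forward applies throughout, so removed women may be kept as not pregnant, which lowers CPR. The article does not define the sets, so the direction is open.
- That one missed session removes a woman. That holds only for acupuncture and moxibustion counted alone and per cycle.

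The sizes rest wholly on assumed rates and can be small. At 2% removal per cycle the shifts are under one point, against a 95% half-width of about 1.96 × √(0.192 × 0.808/100) = 7.7 points with 100 women. If removal is truly unrelated to fertility, an estimate that censors at removal would recover the cumulative rate. The article names no such method and presents categorical outcomes as frequencies and percentages, though an unseen analysis plan could add one. It would still rest on an assumption that follow-up would make unnecessary.

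**Conclusion.** The point holds as a defect in a stated rule. Followed as written, the 70% sentence stops observation of the primary event on the basis of a post-enrolment variable, and the CPR of all enrolled women cannot then be observed. Carrying removed women forward as not pregnant gives a value at or below the truth. Dropping them gives a value above it if removal is unrelated to fertility, or if removed women have the poorer prognosis.

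The size is unknown. Under the assumptions shown it runs from about +0.5 or −0.9 points (7 women in 100 removed) to about +2.8 or −4.2 points (32 removed). What makes it worth correcting is less the size than that the loss is avoidable, cannot be repaired afterwards, and is not shared by the literature comparator. The undefined unit of the 70% is a second, smaller defect: three hospitals could apply it differently.

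**What to change.** - Separate stopping study treatment from leaving the study. Any rule on stopping treatment is for the authors to state.
- Use compliance only to define the per-protocol set.
- Follow every enrolled woman for pregnancy through the 3 observation cycles, and to delivery if pregnant, whatever her compliance. Keep all of them in the full-analysis-set CPR.
- Have the authors reconcile the 70% and the 80% to 120% figures, and state the unit (per visit, per cycle or cumulative) and how the three treatments are combined.

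The cost is a protocol amendment and some follow-up work. Telephone contact is already used for adverse events (section 2.11), but a call alone does not establish the outcome, because section 2.6.1 requires ultrasound confirmation; the scan result must be collected too. CPR may also be diluted by poor compliers. The per-protocol analysis remains available to show the rate in women who took the treatment.

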### Adverse events

2.11

Any physical or clinical changes will be reported by practitioners, coordinators, and patients in the CRF at each visit and/or by telephone. All related symptoms, date of onset, and duration will be recorded in the CRF. If an adverse event is severe and associated with the trial, we will provide appropriate medical care, and the participant may be withdrawn from this study in such cases. In the case of herbal medicines, slight digestive disorders may occur in some patients. In relation to herbal medicines, some digestive disorders may appear in some patients.^[22]^ In acupuncture treatment, some patients may have mild bleeding and ecchymosis.^[23,24]^ Moxibustion treatment may result in erythema, mild burns, and allergic reaction in some patients.^[24,25]^ However, there are no expected severe adverse events, which are defined as death, life-threatening adverse experiences, hospitalization or prolongation of existing hospitalization, persistent or significant disability/incapacity, or the potential for a congenital anomaly/birth defect resulting from pregnancy.

### Ethics

2.12

This study protocol was externally peer reviewed by the Korean Health Industry Development Institute. Additionally, the trial was authorized by the Institutional Review Board of Dongguk University Ilsan Korean Medicine Hospital (approval number: 2016-01), Kangdong Kyunghee Korean Medicine Hospital (approval number: KHNMCOH2016-04-004-002), and Wonkwang University Kwangju Korean Medicine Hospital (approval number: 2016/1). All recruited patients will provide informed consent before enrollment. This trial is registered with the Korean Clinical Trial Registry (CRIS), Republic of Korea: KCT0002235.

## Discussion

3

Recently in Korea, infertile patients have been highly dependent on ART. Since the government supports the cost of ART based on income from 2006,^[26]^ the number of patients who select ART are increasing annually.^[27]^ The number of infertile patients who are supported by the cost is increasing, as is the financial burden borne by the government. However, the pregnancy rate and success rate of ART are at a standstill. Furthermore, there are side effects associated with ART. During ART, ovarian hyper-stimulation is often performed using an ovulation inducer, which causes ovarian hyperstimulation syndrome (OHSS).^[28,29]^ As the number of infertile patients using ART increases, the incidence of OHSS is also increasing.^[30]^ Previous studies have also shown that maternal complications and adverse pregnancy outcomes such as preterm labor, premature birth, and low birth weight are increasing because of twin pregnancies after ART.^[31]^

Since ancient times, Korea has been influenced by Confucianism; therefore, it has been important to focus on the blood-centered social structure. Pregnancy and delivery have been the greatest factors in supporting the blood-centered society.^[32]^ Accordingly, in Korea, the treatment of infertility using herbal medicines, moxibustion, and acupuncture has been developed. Recently, KM therapies have been confirmed to be effective at improving the general function, endocrine, and reproductive function of women, and they are currently being used as supplementary therapy in addition to ART.^[14]^

However, no clinical trials have confirmed the effectiveness and safety of standard KM therapies for infertility. Because of this, KM has not been recognized as a standard treatment for infertility, and it has been excluded from national projects.

In this study, we will set up standard prescriptions according to the menstrual cycle on the basis of various studies and the prescriptions applied for infertility in Korea's representative large Korean medicine clinics. The standardized comprehensive treatment that can be applied to infertile women will be set up by combining herbal medicine, acupuncture and moxibustion. Overall, the ultimate purpose of this trial is to evaluate the effectiveness and safety of KM treatment for unexplained infertility and to evaluate the cost-effectiveness relative to ART. A total of 100 patients will be classified by age group, after which they will receive herbal medicine treatment according to patient's menstrual cycle and the CPR, IR, OPR, and live birth rate will be evaluated. To confirm the safety of KM treatment, we will check for adverse events every visit. Moreover, to evaluate cost-effectiveness, we will compare the economical effectiveness with that of ART.^[33]^

It should be noted that this trial has limitations. Specifically, it is based on a single treatment group without a blind, randomized control group. Because people usually do not want to wait to conceive, it is not easy to set up a control group. Therefore, literature pertaining to ART will be collected and used to replace a control group to compare the effectiveness and cost-effectiveness. This study is funded by the Ministry of Health and Welfare and the Korea Health Industry Development Institute and the results will be grounds for national policy projects. Moreover, to compare the effectiveness and economics of ART, the recruitment was based on the percentage of assisted reproductive costs supported in the country in 2010.

Despite these limitations, this clinical trial is the first to obtain an objective basis for the effectiveness and safety of KM treatment. The cost comparison with ART is expected to confirm the economic feasibility of Korean medicine treatment, which will allow us to offer a new direction in the treatment of infertility treatment, which is biased toward ART in Korea. We also expect it to be used globally as an alternative to solve the unexplained infertility.

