## Background

1

Infertility is a condition in which successful pregnancy has not occurred, despite normal intercourse over 12 months. Approximately, 9 to 18% of normal couples are infertile.^[1]^ In recent years, the number of elderly pregnancies has been increasing because of changing social trends. Moreover, infertile females are increasing due to stress, obesity, lack of exercise, and environmental pollution.^[2]^ The causes of female infertility are classified as ovulation factors, tubal and peritoneal factors, cervical factors, uterine factors, immunological factors, infection factors, and unexplained. Among these, unexplained infertility is estimated to occur in about 15% of patients.^[3,4]^

Since 2006, Korea has begun to support project medical expenses for infertility. Over the last 10 years, the supporting project for assisted reproductive technology (ART) has grown quantitatively, bringing about 32,000 in vitro fertilizations (IVF) and 30,000 intrauterine insemination (IUI) treatments annually. The total cost of the project is 85.7 billion won; however, the clinical pregnancy rate (CPR) is about 33.5% for IVF and 10% for IUI, which is not very different from 10 years ago.^[5,6]^

Korean medicine (KM) has long utilized acupuncture and herbal medicine treatment for the treatment of infertility.^[7]^ Specifically, KM is widely used as a primary or adjuvant therapy of infertility in Korea and to improve the success rate of ART.^[8–10]^ Many investigations of KM treatment for infertility have been conducted in Korea; however, most investigations of KM treatment were experimental studies, case reports, retrospective chart reviews, and questionnaire studies.^[11,12]^ Several projects recently conducted by local governments and the association of Korean medicine revealed that the results of KM to treat infertility were comparable with IUI.^[7,8,13,14]^ However, many of these studies did not employ standardized KM treatments for unexplained infertility. Moreover, very few studies have been conducted to collect evidence of KM treatment effects on unexplained infertility.^[15]^

Therefore, we have developed a protocol for presenting standard KM treatment of infertility, as well as confirming the effectiveness and safety of KM treatment of unexplained infertility and providing an economic evaluation when compared with ART.

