#### Exclusion criteria

2.4.2

(1)Unable to take herbal medicine, acupuncture, and moxibustion treatment during 4 menstruate cycle treatment periods;(2)Unable to participate in this clinical trial for 7 months;(3)Takes pregnancy-related medicine (e.g., hormones, other herbal medication, etc);(4)Planning to undergo artificial insemination or IVF;(5)A has irregularly menstruating occurring at intervals of less 21 days or more than 40 days(6)Male factor infertility;(7)Has ovulation factor infertility (polycystic ovary syndrome, thyroid disease, hyperprolactinoma, etc);(8)Has tubal or peritoneal or uterus factor infertility (endometriosis, pelvic inflammatory disease, uterine myoma, adenomyosis, etc);(9)Is diagnosed with dampness heat, kidney yin deficiency;(10)Has taken IVF than 4 times;(11)Has severe neuropsychological disease history;(12)Has a severe disease related to infertility (e.g., hypertension, diabetes, chronic/acute hepatitis, hyperlipidemia, cardiovascular disease, cancer, chronic/acute inflammatory disease, etc);(13)Has cancer history within 5 years;(14)Has a skin disease over an acupuncture/moxibustion point;(15)Has an allergy or hypersensitivity to treatment (herbal medicine, acupuncture, moxibustion);(16)Is planning to participate in another clinical trial within 3 months;(17)Does not have the ability to fill out forms.

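### The clinical pregnancy rate builds up over several cycles but has no stated denominator or window, and the planned comparison with ART literature fixes no common unit

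*Protocol article*

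**What the plan says.** The trial has a single arm of 100 women. The Discussion names what stands in for a control: "literature pertaining to ART will be collected and used to replace a control group to compare the effectiveness and cost-effectiveness".

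On exposure, section 2.2 (Design/setting) states: "They will undergo an approximately 4 menstrual cycle treatment period and a 3 menstrual cycle observation period". The exclusion criteria (2.4.2) agree with this, since one of them reads "Unable to participate in this clinical trial for 7 months". Regular intercourse is an inclusion criterion (2.4.1), and women who plan insemination or IVF are excluded (2.4.2), so every cycle is a chance of unassisted conception.

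On the endpoint, section 2.6.1 defines a clinical pregnancy as "at least 1 gestational sac with fetal heart activity confirmed by ultrasound scan 5 to 6 weeks after pregnancy". It gives no denominator for the rate and no period over which pregnancies count. Section 2.8 adds only that "categorical data will be presented in frequency and percentage". By contrast, section 2.6.2 does give a denominator for the ongoing pregnancy rate.

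On ART, the Background describes a national programme "bringing about 32,000 in vitro fertilizations (IVF) and 30,000 intrauterine insemination (IUI) treatments annually" and then says that "the clinical pregnancy rate (CPR) is about 33.5% for IVF and 10% for IUI". It also reports that earlier projects found that "results of KM to treat infertility were comparable with IUI".

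**The concern.** A percentage of women followed over several cycles and a percentage of procedures measure different things. The first rises with each added cycle even when the chance per cycle is low, while the second refers to one attempt. If the trial's CPR is set against ART rates per procedure, the contrast favours Korean medicine (KM) because of the length of follow-up, not because of any effect.

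This matters because the literature comparison is the only basis in the design for a statement about effectiveness relative to ART, and the Discussion says that the results will inform national policy. The Background already reads earlier KM results as similar to IUI, so this is a comparison that readers will make.

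**Working it through.** **Plan's own figure.** The sample size of 100 (5 + 40 + 40 + 15 by age group, section 2.6.3) was set by the funder without a statistical calculation. There is no assumed CPR to reproduce; 100 is used below as the number of women.

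**Inputs**
- Cycles per woman: 4 treatment + 3 observation = 7 (section 2.2). The case of 4 cycles is also shown, because section 2.6.1 fixes no window.
- ART figures shown: 33.5% (IVF) and 10% (IUI), from the Background. They are read as per procedure because of where they stand; the text does not label them.
- Background conception rate per cycle: not in the document. Assumed range 0.5% to 5%.
- Model: a constant, independent chance p in each cycle. Differences between women and dropout are ignored.

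**Step 1: from a cumulative rate C to a rate per cycle.** p = 1 − (1 − C)^(1/k).
- C = 10%: k = 7 gives 1 − 0.90^(1/7) = 1.49%; k = 4 gives 1 − 0.90^(1/4) = 2.60%.
- C = 33.5%: k = 7 gives 1 − 0.665^(1/7) = 5.66%; k = 4 gives 1 − 0.665^(1/4) = 9.70%.
- Example: an observed CPR of 14% over 7 cycles looks better than 10%, but is 1 − 0.86^(1/7) = 2.13% per cycle, about one fifth of 10% per procedure.

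**Step 2: from a rate per procedure to a cumulative rate.** 1 − (1 − q)^k with q = 10% gives 27.1% after 3 attempts, 34.4% after 4 and 52.2% after 7. This only shows how much the unit matters; the document does not say that a woman would have that many IUI procedures.

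**Step 3: no treatment effect, 100 women.** C = 1 − (1 − p)^k. The chance of at least 10 pregnancies is the exact binomial upper tail with n = 100 and probability C.

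| Assumed background rate per cycle | C, 7 cycles | Chance of ≥10, 7 cycles | C, 4 cycles | Chance of ≥10, 4 cycles |
|---|---|---|---|---|
| 0.5% | 3.4% | 0.2% | 2.0% | <0.1% |
| 1% | 6.8% | 14% | 3.9% | 0.6% |
| 1.5% | 10.0% | 55% | 5.9% | 6.9% |
| 2% | 13.2% | 86% | 7.8% | 25% |
| 3% | 19.2% | 99.6% | 11.5% | 72% |
| 4% | 24.9% | >99.9% | 15.1% | 95% |
| 5% | 30.2% | >99.9% | 18.5% | 99.4% |

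**Step 4: the IVF figure.** To exceed 33.5%, at least 34 of 100 women must conceive. Over 7 cycles with no treatment effect, the chance is about 2.6% at a background rate of 4% per cycle and 23% at 5%. Background conception alone is much less likely to reach this level.

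**The case against.** The strongest reply is that the document does not commit to the mismatched comparison. The 33.5% and 10% appear only in the Background, to describe a funding programme. The literature for the comparison is still to be collected, and its unit and horizon are open. The unit of the two rates is not stated, and the sources behind them are not at hand. The 7-cycle window is not stated either, and the visit tables that might show it are missing from the text available. How a literature comparison is harmonised is also something that an article may leave to the full protocol. Finally, the lack of a control is admitted, and the age quotas were chosen with ART in mind.

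Much of this stands, and it limits the point. A reader might infer three stronger things that the document does not support:
- That the plan will set the CPR against exactly 33.5% and 10%. These are the only rates shown, but the Discussion does not name them.
- That an ineffective treatment will appear to match IUI. This depends on a background rate that the document does not give; at 0.5% or 1% per cycle a match over 7 cycles is unlikely (0.2% or 14%).
- That the cost-effectiveness result is biased. Section 2.9.2 names no effect measure or ratio, and a cost per pregnancy that takes cost and pregnancies over the same course within each arm would be consistent.

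The reply does not remove the core. The article fixes tests, significance level and handling of missing data, and gives a secondary rate its denominator, yet leaves the primary rate without denominator or window while committing it to an external comparison. The admitted limitation concerns blinding and randomisation. A mismatch of units is a separate problem, runs in one direction and can be avoided.

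**Conclusion.** The point holds in a limited form. As written, the plan invites a comparison of a multi-cycle percentage of women with ART rates that appear to be per procedure, and nothing in it prevents this. If that comparison is made, a CPR of 10% would look equal to the quoted IUI figure while being only 1.5% per cycle over 7 cycles, or 2.6% over 4. Without any treatment effect, the chance of reaching 10 in 100 over 7 cycles passes one half at a background rate of about 1.5% per cycle and is 86% at 2%. Counting only 4 cycles moves these thresholds up but does not remove the problem. It is clear for IUI and weaker for IVF.

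The conclusion rests on two inferences, the per-procedure unit and the counting window. It also rests on constant, independent cycles and on an assumed range for background conception.

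**What to change.** - Keep the CPR per woman as the primary outcome, but state its denominator (women in the named analysis set) and its window, reported at cycle 4 and at cycle 7. A per-woman proportion is legitimate and need not be replaced.
- Add the clinical pregnancy probability per cycle, with a 95% CI, from a discrete-time or life-table analysis.
- Compare with ART only on the same unit: per cycle with per procedure, or cumulative per woman with cumulative per woman over the same calendar time. Do not set the multi-cycle percentage against per-procedure ART rates.
- Take ART rates for unexplained infertility, by the trial's age bands, where the literature gives them.
- Use the same unit and horizon for the effect measure in the economic comparison.

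The cost is a change of wording in the protocol or analysis plan and a more specific literature extraction. The cycle of conception must also be recorded during the observation period, if this is not already done; visits on set cycle days (section 2.5.2) should supply it during treatment. No change to recruitment or treatment is needed, so it can still be made while recruitment is ongoing. The headline comparison with ART may turn out less favourable.
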